## **Sample Size and Statistical Power**

**Aim 1:** We conducted a series of power/sample size calculations through a SAS macro ([name], 1995) under realistic alternatives to address impact on MDE. We require 200 randomized subjects per intervention condition to achieve 80% power based on a conservative application of our pilot study findings from the CATCH-IT trial. These calculations assume that in the control group 72% are free from depression after one year follow up and the second year continues to follow the same exponential rate for controls; for intervention the hazard is a constant ratio of 0.62, and an attrition rate of 7% for each of the first 4 quarters and 2% for each of the second 4 quarters. Note that the estimated hazard rate of 0.62 is 2/3 of that we observed in this previous study. There are concerns raised about the use of pilot study data to assess power, even using a

lower value than we observed, so we conducted other power calculations based on the data from a similar study. In their study, they found a departure from exponential and disproportional hazards of intervention over time. Assuming the same attrition rate as we found above, a study with 400 randomized subjects would produce 80% power when the effect of CATCH-IT 3 was only 60% at every interval of time relative to the CBT hazard rate in the Clarke's study. Thus we expect to have sufficient power even if the overall benefit is 60% that obtained by Clarke.

**Aims 2 and 3:** We will examine changes in the growth curve for depressive symptoms and quality of life over 6 measures. We have 80% power to detect a modest effect size of 0.25 by the last time point, accounting for 75% reliability in the intercept ([www.psmg.usf.edu/PowerCal/case0.html](http://www.psmg.usf.edu/PowerCal/case0.html)).

**Aim 4:** Using mean and standard deviation values from our previous educational impairment data as an illustration of moderator analyses with M=11.3 (SD=3.6) and M=9.9 (SD=3.4), with power of 0.80, alpha level of 0.05, and 10% attrition, 109 participants are needed for each group for a total of 218 participants. Thus we have sufficient power to detect moderate to large interactions with intervention.

**Exploratory Aim 1** will consist of calculation of descriptive statistics. For **Exploratory Aim 2**, we will conduct an economic evaluation to determine the potential benefits of both arms the intervention based on and stated preferences (willingness to pay) and value of health improvements (difference in depression free days valued using Quality Adjusted Life Years conversion factor for depression) proceed ahead with a formal cost-effectiveness evaluation if justified.

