| Functionality                                                               | World Health Organization (WHO) Quality of Life Scale (26 items)                                                                                                                                                                                                                                                                                        | P              |          | P        | P        |          | P        |
| Family dynamics (self-report)                                               | Sibling Relationship Questionnaire (48 items)                                                                                                                                                                                                                                                                                                           | P,A            |          |          | P,A      |          | P,A      |
| Family dynamics (self-report)                                               | Child's Report of Parental Behavior Inventory (23 items)                                                                                                                                                                                                                                                                                                | P,A            | A        |          | A        |          | P,A      |
| Family dynamics (Self-report)                                               | Conflict Behavior Questionnaire (20 items),                                                                                                                                                                                                                                                                                                             | P,A            |          | P,A      |          | P,A      |          |

|                                                                                                                                              |                                                                                                                                                                   |                                                                                                   |  |  |   |  |   |

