|----------------------------------------------------------------------------------------------------------------------------------------------|-------------------------------------------------------------------------------------------------------------------------------------------------------------------|---------------------------------------------------------------------------------------------------|--|--|---|--|---|
|                                                                                                                                              |                                                                                                                                                                   |                                                                                                   |  |  |   |  |   |
|                                                                                                                                              |                                                                                                                                                                   |                                                                                                   |  |  |   |  |   |
| Developmental milestones (interview)                                                                                                         | Social Adjustment Scale (36 items)                                                                                                                         | A                                                                                                 |  |  | A |  | A |
| Personalization - Motivation                                                                                                                 | Theory of Planned Behavior Scale (21 items, alpha=0.76 and Trans-theoretical Model scale (4 items, alpha =0.76)                                            | A                                                                                                 |  |  | A |  | A |

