**Trans-theoretical Model Scale** - We will measure motivation to change risk-factor behaviors before, during, and after the intervention. We adapted the standard approach for measuring motivation as described by Miller and Rollnick to evaluate importance (“rate the importance of preventing a depressive episode”), self-efficacy (“rate your ability to learn coping skills to reduce your risk of depression”) and readiness (“rate your readiness to learn coping skills”) on a 1-10 scale (1, “not important”, 10 “very important”).

**Child’s Report of Parental Behavior Inventory (CRPBI)** – A scale used to evaluate a teen’s perceptions and experiences of both mother and father.

**Sibling Inventory of Differential Experience (SIDE)** – A scale to measure a teen’s perceptions of parent (both mother and father separately) responses to the teen as compared to their siblings.

**Motivational Interview Pre-Measure** - This measure is administered to adolescents prior to meeting with the physician for a motivational interview. It contains items asking adolescents to identify goals for the intervention, consider how they are feeling and their degree of motivation to change their feelings, and their willingness to engage in the present intervention. This is an optional measure.

**Suicide Ideation Scale** - A scale used to assess the adolescent’s current level of suicidal tendencies. This measure is only used in response to adolescent reports of suicidal thinking.

**Suicide Intent Scale** – A measure used to inquire about past suicide attempts. This measure is only used in response to adolescent reports of suicidal thinking.

**Lethality Scale** – A measure of the lethality of past suicide attempts. This measure is only used in response to adolescent reports of suicidal thinking.

**Safety phone calls-** Assessment calls to evidence self-harm ideation and adverse experience with Internet program. Qualitative questions regarding website and baseline interview are also included.

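### The quality-of-life power assumes six measurements, but Table 5 schedules the scale four times, with every entry marked for parents

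*Protocol*

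**What the plan says.** Protocol, Sample Size and Statistical Power, Aims 2 and 3: "We will examine changes in the growth curve for depressive symptoms and quality of life over 6 measures". The next sentence gives the result: "We have 80% power to detect a modest effect size of 0.25 by the last time point, accounting for 75% reliability in the intercept". Slope variance, alpha, sidedness and attrition are not stated for these aims.

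Section 2, Hypothesis 3, places the quality-of-life benefit in the youth and tests it through slopes over two years. Section 2 (Approach) and Section 4a (Research Design) list quality of life among the outcomes assessed at 2, 6, 12, 18 and 24 months.

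Table 5 (section L, Assessment instruments) gives the schedule:
- CES-D: an adolescent entry (A) at months 0, 2, 6, 12, 18 and 24.
- "World Health Organization (WHO) Quality of Life Scale": P at months 0, 6, 12 and 24. Months 2 and 18 are blank and there is no A.

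The legend defines A as adolescent, P as parents on the adolescent's site, and P* as parents on their own site. The List of Assessments describes the scale under Adolescent Measures and again under Parent Measures.

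**The concern.** The power sentence names two outcomes and gives both the same number of measurements. The schedule supports that number for one of them. An estimate of a slope draws on the number and spacing of occasions, so a figure derived for six does not carry over to four.

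The respondent matters more. Hypothesis 3 is about adolescents. If sites follow Table 5 as printed, the scale is given to parents at four visits and no adolescent form is scheduled. Analysis cannot recover a self-report that was never collected.

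**Working it through.** **Schedule side by side**

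| Source | Occasions for quality of life | Respondent |
|---|---|---|
| Power paragraph, Aims 2 and 3 | 6 | not stated |
| Sections 2 and 4a | baseline (Section 2) plus 2, 6, 12, 18, 24 | not stated for this scale |
| Hypothesis 3 | slope over 2 years | youth |
| Table 5 | 4 (0, 6, 12, 24) | P only |
| List of Assessments | not stated | adolescents and parents |

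The count of six agrees with Sections 2 and 4a but not with Table 5. The respondent differs between Table 5 and the List of Assessments.

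**Inputs for the power check**
- From the protocol: effect δ = 0.25 at month 24; 75% reliability; 200 per arm ("We require 200 randomized subjects per intervention condition to achieve 80% power", stated for Aim 1).
- Assumed: two-sided alpha 0.05; a linear random-slope model; total variance 1, so that 75% reliability gives residual variance σ² = 0.25.

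**Step 1. Can the stated 80% be reproduced?** Not uniquely.
- Month-24 comparison of means: z = 0.25/√(2/200) = 2.50. Two-sided power is Φ(2.50 − 1.96) = 70.5%. One-sided 5% gives Φ(2.50 − 1.645) = 80.4%, but this does not use the number of measures.
- Growth model with six measures: power runs from 99% to 58% as the standard deviation of the 24-month slope goes from 0 to 1.

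**Step 2. Formula.** z = (δ/24) / √[2(τ + σ²/Sxx)/n] and power = Φ(z − 1.96). Here τ is the variance of the monthly slope and Sxx is the sum of squared deviations of the visit months from their mean.
- Months 0, 2, 6, 12, 18, 24: Sxx = 1084 − 62²/6 = 443.3.
- Months 0, 6, 12, 24: Sxx = 756 − 42²/4 = 315.

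**Step 3. Set six measures to exactly 80%, then remove two.** With n = 200, 80% power needs τ + σ²/Sxx = 100 × [(0.25/24)/2.802]² = 0.001382.
- *σ² = 0.25.* τ = 0.001382 − 0.25/443.3 = 0.000819, a 24-month slope SD of 0.69. With four measures the sum is 0.000819 + 0.25/315 = 0.001612, z = 2.594 and power is **74%**. The effect detectable with 80% power is 0.27.
- *τ = 0, residual variance free.* σ² = 0.001382 × 443.3 = 0.613. With four measures the sum is 0.613/315 = 0.001946, z = 2.36 and power is **66%**. The detectable effect is 0.30. This is an outer bound, since a residual variance of 0.613 no longer matches the 75% reliability as read here.

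**Step 4. Does the 80% already allow for dropout?** Aim 1 assumes "an attrition rate of 7% for each of the first 4 quarters and 2% for each of the second 4 quarters", so 0.93⁴ × 0.98⁴ = 0.69 remain at month 24, or 138 per arm. Counting only those 138 and keeping σ² = 0.25, six measures still give 80% if the 24-month slope SD is 0.47. Four then give 71%. The stated 80% therefore fits a calculation with attrition as well as one without.

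**The case against.** The strongest reply on the respondent is that Table 5 is introduced as an overview followed by a complete list, and that list includes the scale for adolescents. The table is not exhaustive, since the Teen Behavior Questionnaire has no row, and the available copy has blank rows and a truncated entry. P could also mean a parent's report about the adolescent. This stands in part. A reader might infer that youth quality of life will not be measured at all, but the documents do not support that. They show a schedule and a list that disagree. A parent report would still not be self-report, and the list describes the scale as capturing a person's own perceptions.

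On power, the calculator behind the 80% cannot be inspected. A reader might infer a further shortfall because Aim 1's attrition is not repeated. Step 4 shows that this cannot be established.

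Two wider readings also fail. The "Social Adjustment Scale (36 items" entry and the motivation scales appear at months 0, 12 and 24 only, but neither is named in the power sentence. Nor can it be said that no other school-functioning scale exists, given the condition of the table. The motivation text promises measurement "We will measure motivation to change risk-factor behaviors before, during, and after the intervention". CATCH-IT includes a motivational interview at month 12, so months 0, 12 and 24 can be read that way.

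**Conclusion.** The point holds in two parts. First, the six-measure premise is wrong for quality of life, because the schedule gives four occasions. Secondly, the protocol contradicts itself on who completes the scale, and Table 5 as printed schedules no adolescent self-report for an adolescent hypothesis. The second part is the more serious.

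The loss from fewer occasions is moderate: from 80% to about 66–74%, or 6 to 14 points. This assumes a linear slope model, two-sided 0.05, 200 per arm and six measures giving exactly 80%. If only parents complete the form, no power can be stated for adolescent-reported quality of life. Depressive symptoms under Aim 2 keep their six CES-D occasions, so that premise is untouched.

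**What to change.** 1. Reconcile Table 5 with the Adolescent and Parent Measures lists and with Hypothesis 3. State who completes the WHO scale and, for each P entry, whether the parent reports on self or on the adolescent.
2. Add an A entry for the scale at the existing self-assessments that the growth model will use. All six occasions would match the power text; fewer are acceptable if the text is changed to agree.
3. Restate the quality-of-life power separately from depressive symptoms, for the occasions actually scheduled. Give alpha, sidedness, slope variance and the attrition assumed.
4. Bring the assessment months listed for quality of life in Sections 2 and 4a into line.

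Items 1, 3 and 4 are text changes. Item 2 adds a 26-item form to self-assessments that can be completed online. The burden is small but real, because the protocol justifies a streamlined battery. If follow-up is already under way, added entries reach only the visits still to come, and the text should say what has been collected so far.

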## c. Justification for inclusion of any special or vulnerable populations

**Inclusion of Children:** The target age group for this intervention is adolescents ages 13-18. This is a high-risk age group for depression. The intervention requires the adolescent to participate in insight-oriented activities. Younger children may not have yet developed the cognitive ability to complete the exercises and adolescents older than 18 frequently may have already experienced an episode of depression. The goal of this intervention is to prevent the first episode.

**Women, Children, and Minorities:** Based on previous studies at our sites, we anticipate that about 60-70% of the adolescent participants will be female. Because of the emergence of gender differences in depression during adolescence (Hankin et al., 1998), we will test for gender effects in the present study, although in Clarke et al. (2001) there were no differences in the rate of change over time for males and females and no interactions between gender and treatment. We are not studying children younger than age 13 because the CATCHIT-2R intervention would require substantial adaptation for children's developmental needs. Moreover, the risk of depressive episodes is considerably lower for children below age 13 years. Our experience is that the ethnic ratio will reflect that found in the population in the cities in which the primary care practices are located (please see Target Enrollment Form Page). The geographic heterogeneity of the sites (i.e., Boston (Northeast), Chicago (Midwest)) should provide some degree of ethnic diversity. We assume an overall minority representation of about 15%, which is comparable to previous studies at these sites and representative of the populations in the communities served. We plan to over-sample minority participants.

d. Plans for subject selection, recruitment, and documentation of informed consent

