**Longitudinal data analysis:** Our general method will be to use growth curve modeling with continuous outcomes to examine how the intervention changes depressive symptoms, vulnerability factors, educational impairment and quality of life. Simple comparisons will be calculated as appropriate (e.g. number of depressed days), and survival curve modeling will be used for binary outcomes for prevalence of disorders. Guided by our methods development on growth models, we will address missing data using full information maximum likelihood and multiple imputation, which provide improvement over "last observation carried forward" and other less refined methods. We will also examine whether there are variations in growth trajectories by introducing covariate interactions and mixtures to growth models, techniques that we and our colleagues have developed. These more complex models can characterize quantitatively differential response as well as qualitative changes such as recurrence. All such models will be preceded by careful model checking.

**Mediator analysis:** We will evaluate potential mediators including change in motivation, principles (intervention experience characteristics) of effective preventive interventions (adherence/dose, positive relationships, training and socio-cultural relevance) and changes in vulnerability and protective factors (social support, automatic negative thoughts, depressed mood). Based on our recent work on a comparison of analytic models for mediation with nonlinear models, we will use the "product of coefficients" method to conduct tests of mediation and the bootstrap method for accurate confidence intervals. To examine the effects of participating in the website, we will conduct complier average causal effect (CACE) analyses that include covariates predicting participation status.

**Moderator analysis:** We expect to conduct tests of moderation in six domains: (1) demographic and cultural factors, (2) vulnerability factors and adverse events, (3) motivation and attitudes, (4) physician relationship, (5) parent and child co-morbid psychopathology, and (6) treatment before and during study. We will use sub-group analyses and tests of interaction to evaluate moderator effects.

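### The Aim 4 power paragraph is a two-group comparison of means and does not support its claim of sufficient power for moderate interactions

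*Protocol*

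**What the plan says.** Under Sample Size and Statistical Power, the Aim 4 paragraph borrows educational impairment data from the earlier trial, means of 11.3 (SD 3.6) and 9.9 (SD 3.4), "as an illustration of moderator analyses". It sets its conditions "with power of 0.80, alpha level of 0.05, and 10% attrition" and states that "109 participants are needed for each group for a total of 218 participants". The next sentence draws the conclusion: "Thus we have sufficient power to detect moderate to large interactions with intervention".

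The paragraph does not say which two groups the means describe. It gives no moderator prevalence, no subgroup size and no interaction contrast.

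The moderator paragraph of the Data analysis section lists six domains and adds: "We will use sub-group analyses and tests of interaction to evaluate moderator effects". The Specific Aims section makes moderation part of a numbered aim with its own Hypothesis 4A.

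**The concern.** The number comes from one kind of comparison and the conclusion concerns another. A sample size for the difference between two groups says nothing directly about power to detect that a treatment difference varies between subgroups. That second contrast is estimated much less precisely from the same participants.

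What is at stake is how the moderator results will be read. Over-sampling of minority youth is justified by the wish to study whether sources of resilience and vulnerability differ by ethnicity. If the trial is on record as adequately powered for moderate interactions, a non-significant interaction invites the conclusion that the programme works alike in all subgroups. For moderate interactions the data could not support that.

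**Working it through.** **1. Reproduce the stated figure.** The inputs are those of the Aim 4 paragraph. Sidedness is not stated; two-sided 0.05 reproduces the figure, while one-sided gives 78 per group before attrition.

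- Pooled SD = √[(3.6² + 3.4²)/2] = 3.50; difference = 11.3 − 9.9 = 1.4; d = 1.4/3.50 = 0.40.
- n per group = 2 × (1.96 + 0.842)²/0.40² = 98.2, so 99.
- 99 × 1.10 = 108.9, so 109 per group and 218 in total. This matches. (Dividing by 0.90 would give 110 and 220, an immaterial difference.)

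This is the ordinary two-sample formula, with no interaction term.

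**2. Variance of an interaction.** With 1:1 arms, N evaluable and a binary moderator of prevalence p, the difference between the two treatment effects, in SD units, has

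SE = √[4/(N·p·(1 − p))].

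At p = 0.5 this is √(16/N), against √(4/N) for the main effect, so the variance is four times as large.

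**3. Evaluable numbers.** 400 are randomised.

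- With Aim 4's 10% attrition: 360.
- Aim 1 assumes "an attrition rate of 7% for each of the first 4 quarters and 2% for each of the second 4 quarters", so retention is 0.93⁴ × 0.98⁴ = 0.690, or 276.

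**4. Power, even split, unadjusted, one time point.** Power ≈ Φ(δ/SE − 1.96).

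| Evaluable N | SE | δ = 0.40 | δ = 0.50 | δ = 0.80 |
|---|---|---|---|---|
| 218 | 0.271 | 31% | 46% | 84% |
| 276 | 0.241 | 38% | 55% | 91% |
| 360 | 0.211 | 48% | 66% | 97% |
| 400 (no loss) | 0.200 | 52% | 71% | 98% |

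**5. Size needed for δ = 0.40.** N = 16 × (1.96 + 0.842)²/0.40² ≈ 786 evaluable, or 786/0.90 ≈ 873 randomised at 10% attrition.

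**6. Smallest interaction detectable with 80% power.** 2.802 × SE.

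- p = 0.5: 2.802 × 0.211 = 0.59 SD (N = 360); 2.802 × 0.241 = 0.67 SD (N = 276).
- p = 0.15: 2.802 × √[4/(360 × 0.1275)] = 0.83 SD; 2.802 × √[4/(276 × 0.1275)] = 0.94 SD.

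**7. Unequal splits at δ = 0.40.** A 35/65 split, within the expected 60-70% female, gives 35% (276) to 44% (360). A 15/85 split gives 22% to 27%.

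**8. Major depressive episodes.** Aim 1's assumptions give a control hazard of −ln 0.72 = 0.3285 per year and an intervention hazard of 0.62 × 0.3285 = 0.2037. In each quarter let e be a quarter of the yearly hazard and a = −ln(1 − attrition). A participant still at risk then has an event with probability [e/(e + a)] × [1 − exp(−(e + a))]. Summed over eight quarters this is 0.390 and 0.269, so 200 × 0.390 + 200 × 0.269 ≈ 78 + 54 = 132 events. Taking SE of the log ratio of hazard ratios ≈ √[4/(132·p·(1 − p))], the detectable ratio at p = 0.5 is exp(2.802 × 0.348) ≈ 2.7. At p = 0.15 it is about 3.9.

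**The case against.** The best defence is that the protocol never claims 80% power for a 0.40 SD interaction. It offers the data as an illustration and claims power for moderate to large interactions. For large ones it is right: at 0.8 SD the full trial has 91-97% power with an even split and 89-95% with a 35/65 split. Even at 0.7 SD, power is 83-91%. This stands, so the sentence needs limiting rather than reversing.

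A second defence is that the planned analysis is stronger than the one computed above. The Data analysis section provides for covariate adjustment, and for growth models with full information maximum likelihood and multiple imputation, so participants with partial follow-up still contribute. Counting 276 is therefore a pessimistic bound for continuous outcomes. The protocol gives no correlation. If adjustment for a baseline score with correlation r = 0.5 to 0.7 is assumed, the variance is multiplied by 1 − r² (0.75 to 0.51). Power at 0.40 SD becomes 48-64% with 276 evaluable and 59-76% with 360. That is better, but still below 80%.

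Three stronger readings are tempting and the document does not support them.

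- The 10% in Aim 4 and the 31% implied by Aim 1 may look like a contradiction. Aim 1's figure is cumulative loss over 24 months, while the Aim 4 paragraph names no time point. The two may refer to different horizons, so both are carried here as scenarios.
- The minority subgroup may look fixed at 15%. The protocol says "We assume an overall minority representation of about 15" per cent, but the same paragraph plans to over-sample minority participants. The 15/85 figures describe a case without over-sampling.
- The trial as a whole may seem underpowered. The 400 randomised rests on the Aim 1 calculation, which this point does not touch.

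The status of the moderator analyses is also mixed: the Executive Summary and the Research Design summary list moderators among exploratory analyses, while the Specific Aims section gives them a numbered aim.

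**Conclusion.** The Aim 4 calculation is a main-effect calculation, and its concluding sentence does not follow from it. This is so whichever two groups the means describe, because on any reading they form a single two-group difference. It is an error in a stated property of the design rather than detail left for a later document.

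The 31% belongs to the stated 218, and the 38-48% to the full trial after attrition. All these figures assume an interaction equal to the 0.40 SD shown, a 50/50 binary moderator (the most favourable split) and an unadjusted single-time-point analysis. They should not be quoted as fixed properties of the trial. Taking 0.5 SD as moderate and 0.8 SD as large, which is a convention and not a definition in the protocol, the claim fails for the first and holds for the second when the moderator is reasonably balanced.

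Severity is should-fix: recruitment, the primary analysis and participant safety are unaffected.

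**What to change.** Replace the 218 calculation with an interaction calculation at N = 400.

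- State the attrition and the time point it refers to, the moderator split, and any assumption about covariate adjustment or repeated measures.
- Give the smallest interaction detectable with 80% power. Without adjustment this is about 0.59-0.67 SD at 50/50 and about 0.83-0.94 SD at 15/85, the latter labelled as a scenario without over-sampling. For major depressive episodes with about 132 events it is a ratio of hazard ratios of about 2.7 at 50/50.
- Limit the statement of sufficient power to large, reasonably balanced interactions.
- State that moderator results will be reported as estimates with confidence intervals, and that a non-significant interaction will not be taken as evidence that the effect is the same across subgroups.

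The cost is a change of text and a less favourable power statement. No change to sample size, recruitment or conduct is needed.
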